### Statistical Analysis

#### Pre-Processing of Electroencephalogram Data

The actual electroencephalogram signals are recorded using a six-channel configuration at F7, F8, T7, T8, O1, and O2 (Emotiv EPOC® Headset -EMO-EPO-BT9X-03). Lakshmi et al. (41) pointed out that the acquired brain signals are contaminated by noise and artefacts (e.g., eye blinks, eye movements and heartbeat). Besides, interference of muscle movements and power lines are also mingled with brain signals (42). Meanwhile, artefact avoidance is an effective preventive method to minimize artefacts by instructing participants to try to avoid unnecessary blinks, hand/body movements. Therefore, it is necessary to remove artefacts from EEG signals by filtering and feature extraction process.

At first, wavelet denoising is used to preprocess the raw data. By eliminating high frequency, the wavelet method is performed to obtain the finer signal and enhance the effect of noise removal of artefacts (43). Then, a sixth-order band-pass filter with cut-off frequencies of 3 Hz and 13 Hz used in this study to filter the denoised EEG signals. Its purpose is to filter the electromyogram artefacts that tend to remove the unimportant information from high-frequency bands and electrocardiogram that tend to dominate the low-frequency. The next process is feature extraction. Previous studies suggested that principal component analysis is an efficient method the feature extraction (44). Finally, the results of the feature extraction principal component analysis then processed to obtain electroencephalogram spectra of normal condition.

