**Methods:**

This program is a single-blinded, randomized, prospective clinical trial to test the effect of process-based multi-task cognitive training in older adults with MCI. Ninety participants with MCI will be recruited and randomly assigned to the cognitive training group (n=45) and the wait-list control group (n=45). The cognitive training group will receive 10 weeks of process-based multi-task cognitive training and health education twice a week, at 40~60 min per session. While the wait-list control group will only receive 10 weeks of health education during the research period. The effect is measured using the executive function, neuropsychological assessment performance and related brain activity assessed with electroencephalogram parameters (slowness and complexity of the EEG) at baseline, after 10 weeks of training, and a 3-month follow-up.

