The secondary outcome measures include neuropsychological assessments, transfer effect and electroencephalogram acquisition. Neuropsychological assessments are as follows: (1) the composite z score for the overall cognitive function, including the questionnaire of MoCA (38); (2) the Psychomotor speed, which will be accessed by Finger Tapping Test (37) and Reaction Time test (39). The transfer effects measure consist of fluid reasoning and working memory. Two tasks will be used to measure working memory: digit span forward and backward from the Wechsler Adult Intelligence Scale-Revised. Raven’s Advanced Progressive Matrices (RAPM) will be used to assess fluid reasoning. The electroencephalogram data will be recorded and collected using the Emotiv EPOC® Headset (EMO-EPO-BT9X-03) with 14 channels mobile (AF3, F7, F3, FC5, T7, P7, O1, O2, P8, T8, FC6, F4, F8, and AF4) and two references (CMS/DRL references at P3/P4; left/right mastoid process alternative). The parameters are as follows: the sampling rate is 128 Hz, the resolution is 14 bits with 1 LSB (= 0.51μV), and bandwidth is 0.16–43Hz (digital notch filters at 50Hz and 60Hz). The recording time will last approximately 5 min. The participants will be required to close and open their eyes for 30 s, respectively. During data acquisition time, the participants will be told not to move their hands and other parts of the body (40).

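### Eye blinks are named as an EEG contaminant to be removed, but no described pre-processing step targets them, so a frontal eyes-open slowness index can partly reflect blinking

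*Protocol article*

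**What the plan says.** All references are to the protocol article.

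The abstract (Methods) gives the EEG parameters as "slowness and complexity of the EEG", without a formula. Outcome Measurement lists EEG among the secondary outcomes and gives a 14-channel headset sampled at 128 Hz, with a recording of about 5 minutes. On eye condition it says: "The participants will be required to close and open their eyes for 30 s, respectively". It does not say which period enters the analysis.

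Pre-Processing of Electroencephalogram Data says that signals are recorded from six sites (F7, F8, T7, T8, O1, O2) and that "the acquired brain signals are contaminated by noise and artefacts (e.g., eye blinks, eye movements and heartbeat"; muscle and power-line interference are added next. Prevention comes first: "artefact avoidance is an effective preventive method to minimize artefacts by instructing participants to try to avoid unnecessary blinks, hand/body movements". Removal follows: "Therefore, it is necessary to remove artefacts from EEG signals by filtering and feature extraction process". The steps are then given in order:

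- Wavelet denoising: "By eliminating high frequency, the wavelet method is performed to obtain the finer signal".
- A band-pass filter of order six, passing 3 to 13 Hz, whose stated purpose covers electromyogram and electrocardiogram.
- PCA, because "principal component analysis is an efficient method the feature extraction".
- Spectra computed from the PCA result.

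**The concern.** The section promises removal of artefacts that include blinks, then sets out a complete sequence with no step directed at them. A blink is a slow, large, mainly frontal pulse. Two of the six sites, F7 and F8, are frontal, and part of the recording is made with the eyes open. After a 3-13 Hz filter, any frequency-based slowness index has to use the lower part of that band, which is where a blink residue would fall.

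At stake is the tertiary aim, which reads EEG change as brain activity underlying the training. Blink rate and size vary between people and visits. If they leak into the index they add noise, and a change in blinking could be taken for a neural change.

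**Working it through.** **Step 1. Match each step to its stated target.**

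| Step | Stated target | Effect on a blink |
|---|---|---|
| Instruction | Unnecessary blinks, hand and body movement | Preventive only; Outcome Measurement mentions only hands and other body parts |
| Wavelet | High frequency | Little, because the pulse is slow |
| 3-13 Hz filter | Muscle and heart signals | Removes most energy, through the 3 Hz edge |
| PCA | Feature extraction | None specified; no rejection rule |

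**Step 2. How much blink energy passes the filter.** The documents give no blink figures, so there is none to reproduce. From the documents: 128 Hz sampling, 0.16-43 Hz bandwidth, the 3-13 Hz pass band and order six. Assumed: a Butterworth design, and the pulse shape and width.

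Share kept = (filtered pulse energy over 0.16-43 Hz) / (unfiltered pulse energy over 0.16-43 Hz).

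| Pulse | 0.2 s | 0.3 s | 0.4 s | 0.5 s |
|---|---|---|---|---|
| Raised cosine, symmetric | 36.3% | 16.0% | 5.9% | 1.9% |
| Raised cosine, asymmetric | 34.4% | 15.8% | 6.7% | 2.9% |
| Gaussian | 4.0% | 0.5% | 0.1% | 0.0% |

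Width is total duration for the raised cosines and width at half height for the Gaussian, so a 0.2 s Gaussian is the wider pulse. Reading order six as six per band edge lowers the figures slightly (symmetric raised cosine: 35.8% at 0.2 s to 1.0% at 0.5 s). For the raised-cosine pulses, at least 96% of what survives lies below 8 Hz and at most 4% in 8-13 Hz.

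A hand check for a Gaussian pulse with standard deviation s and an ideal 3 Hz edge: share above 3 Hz = erfc(2π × 3 × s). This gives erfc(0.942) = 0.18 for s = 0.05 s, erfc(1.508) = 0.03 for 0.08 s and erfc(1.885) = 0.01 for 0.10 s. A real filter with sloping edges leaks slightly more.

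**Step 3. What this does to a slowness index.** The index is assumed to be theta/alpha = power in 4-8 Hz / power in 8-13 Hz. Each condition is the mean of 30 simulated 30 s six-channel records with 0.3 s asymmetric blinks. Blink weights are 0.5 at F7/F8, 0.12 at T7/T8 and 0.04 at O1/O2. All of these, and the background EEG, are assumed.

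| Blink amplitude | F7, 0/min | F7, 10/min | F7, 20/min | Change, 0 to 20/min |
|---|---|---|---|---|
| 50 µV | 0.85 | 0.89 | 0.90 | 0.90/0.85 = +6% |
| 100 µV | 0.86 | 0.93 | 1.03 | 1.03/0.86 = +20% |
| 200 µV | 0.86 | 1.18 | 1.45 | 1.45/0.86 = +69% |

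At O1 the ratio stayed within 0.84-0.89 with no trend, and at T7 within 0.82-0.90 with almost none. The 50 µV shift at F7 (0.05) is no larger than that scatter. The zero-blink column also approximates eyes-closed data with few or no blinks.

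A second simulation used Gaussian blinks (s = 50-100 ms, 30-100 µV at F7/F8, 10-20/min, frontal background about 9-10 µV RMS) and 3-8 Hz power. Blink energy kept was 1.5-19%, and F7/F8 slow power rose by anything from 2% to about 4-fold. In its middle case (60 µV, 80 ms) the rise was 15% at 10/min and 33% at 20/min, so doubling the blink rate alone gives 1.33/1.15 = 1.16, or +16%.

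**Step 4. PCA.** In the Step 3 records the blink signal loaded mainly on the first two components: absolute correlations at 20/min were 0.15 and 0.17 at 50 µV, 0.29 and 0.39 at 100 µV, and 0.58 and 0.50 at 200 µV. Keeping leading components would keep the blink, and rejecting a blink component would reduce it. The article states neither rule. The wavelet step was not simulated.

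**The case against.** The strongest reply is that the filter already does most of the work: 64% or more of blink energy is removed in every case of the Step 2 table, and about 96% or more for the Gaussian pulses, whatever purpose the text gives the filter. That stands. A reader might infer that the pipeline cannot remove blinks; the calculation shows incomplete removal, not none.

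A reader might also infer that blinks are the main contaminant. The text gives them as one example among several and ranks none. Nor is it shown that the slowness outcome does measure blinking: the index has no formula, four of the six sites are temporal or occipital, part of the recording is eyes-closed, and every blink input is assumed.

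Bias between arms is a further tempting reading. It would need blinking to change differently by arm, and nothing in the article suggests that. The abstract describes the trial as single-blinded, and Outcome Measurement says that data evaluators are blinded. It would likewise go too far to say that PCA retains the blink, since no retention rule is given.

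Finally, a journal article condenses, and an EEG manual may hold more. This limits the point but does not remove it. The finding is not that detail is absent. The article sets out an ordered sequence from first step to last, and that sequence is not matched to artefacts that the same section says must be removed.

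**Conclusion.** The point holds in limited form. The described steps do not target the ocular artefacts the section sets out to remove. Roughly 1-36% of blink energy remains for finite pulses of 0.2-0.5 s, and 0-4% for smooth Gaussian pulses of that width at half height. The residue lies mainly below 8 Hz, so in eyes-open data it pushes a slowness index at F7/F8 towards slowing, by an amount from negligible to large depending on blink size and rate. It is small at temporal and occipital sites and with eyes closed.

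The consequence is mainly noise in a secondary outcome serving the tertiary aim. It becomes bias only with differential change in blinking. The executive-function result is not touched. The sizes rest on assumed blink shapes, amplitudes, rates, scalp weights and background EEG, and on theta/alpha or 3-8 Hz power as the reading of slowness.

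**What to change.** Add an ocular-artefact step before the wavelet and band-pass steps, with its rule fixed before allocation is revealed:

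- Reject 1-2 s epochs in which a frontal channel exceeds a fixed amplitude limit. This is feasible with F7 and F8 alone. Alternatively, use regression or ICA if all 14 channels in Outcome Measurement are in fact recorded.
- Reconcile the 14-channel list with the six-channel statement in the pre-processing section, since the choice of method depends on it.
- Compute slowness and complexity from the cleaned signals, separately for eyes-closed and eyes-open periods, and do not count PCA feature extraction as artefact removal.
- Give the blink instruction in the acquisition paragraph too, so that the two sections agree.
- Report retained epochs by arm and visit.

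The cost is wording and a short routine in MatLab, which is already named, with no new recording for the F7/F8 option. The real downside is lost data. At an assumed 10-20 blinks/min, a 30 s eyes-open period holds 5-10 blinks. If each spoils one epoch, 5-10 of 30 one-second epochs are lost (17-33%), or 5-10 of 15 two-second epochs (33-67%). A blink across a boundary costs two. Shorter epochs therefore lose less.

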#### Statistical Considerations

The primary and secondary outcome measures were analyzed using data from the intention-to-treat. Moreover, the protocol set principle was defined as those participants or the participants who completed at least 80% adherence to the program initially formulated and assessments all the required will be included. We will compare the characteristics of the completed participants versus dropout ones. Sensitivity analyses of completed participants will be further performed to explore the potential for dropout participants, and the results will be categorized as bias. Listwise deletion will be adopted to estimate treatment effects and sensitivity of the cluster dropout if missing values satisfy the criteria of the losing data entirely at random; otherwise, multiple imputation data strategies will be adopted.

Data processing and statistical analysis will be conducted using SPSS 21.0 and MatLab (The Mathworks Inc. 2016). Descriptive statistics will be reported as frequencies for categorical variables and means ± standard deviations for continuous variables. The adoption mainly the method of exploratory analysis to examine the distribution state of data. The proportionality of baseline data for both groups is compared by the non-parameters Wilcoxon test, chi-square test, and t-test. Regarding the primary outcome, a repeated ANOVA test will be used to evaluate the differences of changes and long-term effect in outcome measurement index performance in the cognitive training group and the wait-list control group, within-group over time, and interaction effects. The simple effect analysis will be added when there is an interaction between intervention factors and time factors. Secondary outcomes will be analyzed using similar statistical methods. The mediating effect model was used to test the transfer effect of cognitive training on untrained cognitive domains, with cognitive training as the mediator. A significant statistical will be considered as P < 0.05 for all comparisons. The effect size (r) was calculated using Cohen’s d to estimate the between-group effect sizes.

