The calculation of sample size is based on the change in executive function after 10-week, which is the primary outcome variable in this study. A meta-analysis found that significant benefits of cognitive training are superior to the wait-list and the effect size of executive function training used to calculate the sample size is 0.575 [0.093,1.056] (18, 19). Sample size estimation was conducted using statistical software G*power. In the analysis with an independent t-test using a power of 80% and a type 1 error of 5%, the calculated total sample for this study is 78. Considering a 15% dropout rate and maximum to ensure the credibility of the cognitive training, we will recruit 46 participants in each group. Thus, the total required sample size for this study is 92 participants.

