### Study Intervention

#### Implementation of the Cognitive Training Program

Participants in the cognitive training group will receive 10 weeks of the process-based multi-task cognitive training program with 60 min group training sessions (a small group of six participants) each given three times per week. This cognitive training program consisted of eleven training tasks in total, with a varying degree of overlap between tasks. The tasks are divided into three categories: 1) warm-up exercise; 2) practice in order; and 3) expanding training (**Table 2**). The task of warm-up exercise lasting 10 min, practice in order and expanding training tasks lasting 50 min. All cognitive tasks are completed within a medical university setting supervision of postgraduate in Master of Nursing Specialist. The program ensures that the ratio of a participant-to-researcher is no greater than 6:1 (6 participants per researcher). Each training task for all nursing specialists was randomly assigned. During the training period, the participant will have an identical training schedule. To balance the social-interaction effect, participants in the cognitive training group participated in the same health education program as the wait-list control group. Participants were reminded via smartphone to complete their training program if missing over 2 weeks. Besides, we develop a training paper record form, and the training record can be checked.

**Table 2 T2:** Tasks of process-based multi-task cognitive training program.

Categories	Tasks	Targeted domain	Difficulty levels/rounds	number of hours	A brief description of the tasks
Warm-up exercise	Recall the names	Memory	0/20	10min	Firstly, introduce yourself one by one (i.e., name, age, occupation). Then, inform participants to remember these names. The participants are asked to write down the names of the other five on white paper according to their memory at the end of cognitive training.
	You act I guess	Working memory	0/1		Firstly, participants were divided into three groups of two. Then, one participant facing the audience uses the most accurate body language to express the meaning of words, while other participants with their backs to the audience are asked to guess those words. Each group is limited to 2 min.

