#### Control Intervention

Participants in the control group are on the waiting list and will receive 10 weeks of health education classes twice a week, at 40~60 min per session. The wait-list group will access to attend the same after the group had completed a 3-month follow-up. The items of health education included the disease knowledge of MCI, physical activity, cognitive activities and social activity. Participants were reminded via smartphone to complete their training program if missing over 2 weeks.

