#### Study Procedure

Participants will be enrolled from the nearby community health service centre via open recruitment through paper flyers, online forums, and word-of-mouth. Participants who interested in this program will be invited for an in-person interview to complete a screening questionnaire in the community health service centre, including demographic characteristics, MMSE, MoCA, ADL, and Achromatopsia anomalous trichromatic test (AATT). A trained physician in community health service centre will invite the potential participants to undergo a physical examination and neurologic diagnosis of MCI. Participants who met the eligibility criteria will be assessed with a baseline assessment and then given the EEG evaluation in the 2 days preceding the start of the cognitive training.

After that, according to the random allocation sequence, participants will be randomly assigned to one of two groups with a targeted assignment ratio of 1:1. The random allocation sequence with a block size of four will be generated using a computer randomization list by an independent researcher assistant. The random allocation sequence is sealed in opaque envelopes by an assistant. The cognitive training group will receive cognitive intervention and health education, whereas the wait-list control group will only receive health education during the research period. During the 3 months follow up, the cognitive training group and wait-list control group will receive no interventions. Complete all outcome assessments, participants in the wait-list control group will be permitted to undergo the process-based multi-task cognitive training program. Although it was not initially the plan, the health education manual for mild cognitive impairment will be provided for participants who are not finishing the cognitive training or health education through various means, such as email, public platform, and short messaging service. All outcome measurements will be assessed at baseline, 10 weeks and 3 months follow up. Study assessments and timelines are illustrated in **Table 3**.

**Table 3 T3:** Summary of study assessments and timelines.

Time point	Measurement	Post-allocation					Mode of Administration
		Baseline	Training sessions	10 weeks assessments		Follow-up 3 months	
		T0		T1		T2	

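### The protocol set applies one 80% adherence cut to two different programmes and, read naturally, makes the 10-week comparison depend on the 3-month visit, so it can be selected differently by arm

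*Protocol article*

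**What the plan says.** Statistical Considerations names intention-to-treat first: "The primary and secondary outcome measures were analyzed using data from the intention-to-treat". It then adds a protocol set, of which it says that "participants who completed at least 80% adherence to the program initially formulated and assessments all the required will be included". The rule is the same for both arms and for every analysis. The section also plans a check of completers against dropouts ("We will compare the characteristics of the completed participants versus dropout ones") and calls analyses of completers sensitivity analyses. The Results paragraph of the abstract says that effects will be described under both intention-to-treat and the protocol set.

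The programmes differ. Study Procedure states: "The cognitive training group will receive cognitive intervention and health education, whereas the wait-list control group will only receive health education during the research period". Control Intervention says that controls "will receive 10 weeks of health education classes twice a week, at 40~60 min per session". For training, the Methods paragraph of the abstract gives "10 weeks of process-based multi-task cognitive training and health education twice a week, at 40~60 min per session", while Implementation of the Cognitive Training Program gives "60 min group training sessions (a small group of six participants) each given three times per week" and adds that trainees also attend the controls' health education programme.

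Study Procedure and Outcome Measurement schedule every outcome at baseline (T0), 10 weeks (T1) and 3 months (T2). The trial is sized on the 10-week result: "The calculation of sample size is based on the change in executive function after 10-week, which is the primary outcome variable in this study".

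**The concern.** A protocol set is chosen on behaviour after randomisation. If the choice works alike in both arms, the comparison may stay fair. Here two features of the rule let it work differently.

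First, 80% of training plus classes is not the same hurdle as 80% of classes. Training tasks grow harder as participants improve, and under Difficulty Level those who do not progress for three weeks must try a higher level. If trainees who pass are a more selected group than controls who pass, and adherence is related to change in executive function, the arms differ for reasons other than training.

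Second, if all required assessments include T2, someone who completed the programme and the 10-week assessment leaves the 10-week protocol-set result because of a later absence. Study Procedure offers controls the training only once their outcome assessments are complete. This gives controls a reason to attend T2 that trainees lack.

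At stake is a second reported estimate. Because the abstract announces both sets without ranking them, a favourable protocol-set result could be read as equal in weight to a weaker intention-to-treat result.

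**Working it through.** **The plan's own figures.** The article gives no figure for the protocol set. The nearest are the sample size figures: d = 0.575, 80% power, 5% type 1 error, total 78, then 92 after 15% dropout. An exact noncentral t calculation gives 39 per arm, or 78 in total (power 0.808), with a one-sided 5% test. A two-sided test needs 98. The article does not state the sides; that is a separate matter. 78/(1 − 0.15) = 91.8, rounded up to 92, agrees. Below, 0.575 serves only as a yardstick.

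**Step 1: what 80% means in sessions.**

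| Component | Planned over 10 weeks | 80% |
|---|---|---|
| Control classes (Control Intervention) | 2 × 10 = 20 | 16 |
| Training, abstract | 2 × 10 = 20 | 16 |
| Training, Implementation section | 3 × 10 = 30 | 24 |
| Training plus classes pooled, Implementation section | 30 + 20 = 50 | 40 |

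The training threshold is therefore 16 or 24 sessions depending on the section, and 40 if classes are pooled with training. On the abstract's wording, training sessions and control classes are equal in number.

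**Step 2: does the count alone matter?** Assume that everyone attends each session independently with probability 0.85. The binomial chance of passing is 0.830 for 16 of 20, 0.847 for 24 of 30, and 0.880 for 40 of 50. If trainees must reach both 24 of 30 and 16 of 20, it is 0.847 × 0.830 = 0.703. More sessions do not by themselves make the cut harder at this attendance. The counting rule does matter, and so would lower attendance at the more demanding sessions.

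**Step 3: selection bias when there is no true effect.** Let adherence propensity be standard normal and let the outcome correlate ρ with it. If the top fraction p of an arm passes, the mean propensity among those who pass is m(p) = φ(z₁₋ₚ)/p. The spurious difference, training minus control, is ρ × [m(p_T) − m(p_C)]. The values are m(0.90) = 0.195, m(0.85) = 0.274, m(0.80) = 0.350, m(0.75) = 0.424 and m(0.60) = 0.644. Pass rates and ρ are assumptions; the article gives neither.

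| Pass rate, training / control | ρ = 0.2 | ρ = 0.3 | ρ = 0.4 |
|---|---|---|---|
| 85% / 85% | 0 | 0 | 0 |
| 80% / 85% | 0.015 | 0.023 | 0.030 |
| 75% / 90% | 0.046 | 0.069 | 0.091 |
| 60% / 90% | 0.090 | 0.135 | 0.180 |

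The non-zero values run from 0.015/0.575 = 2.6% to 0.180/0.575 = 31% of the planning effect. The sign reverses if controls are the more selected arm, or if ρ is negative.

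**Step 4: the T2 condition.** The plan allows for 92 − 78 = 14 losses and does not say when they fall. If all 14 occur before T1, the T2 condition removes nobody further from the 10-week comparison. If all occur after T1, it could remove up to 14 people who have the 10-week outcome. The article does not narrow this range.

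**The case against.** The strongest reply is that nothing primary rests on this set. Intention-to-treat leads, the protocol set is an addition, and completer analyses are called sensitivity analyses. Selection after randomisation is a known limit of every per-protocol set, and applying a percentage to each arm's assigned programme is common practice. This stands and limits the point, although neither the abstract nor Statistical Considerations actually labels the protocol set supportive.

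A second reply is that the section neither says how 80% is counted in each arm nor names the 3-month visit. A condensed article may leave such details to a fuller document. That also stands: including T2 is the natural reading of the assessment condition, but an inference.

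A third is that the T2 condition may add nothing. The planned repeated ANOVA covers all time points, and with listwise deletion anyone missing T2 is lost regardless. This is right on that path, so relaxing the set definition alone would not bring those participants back. On the multiple-imputation path, the protocol-set rule would still exclude them.

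A reader might go further and infer that the rule does favour training, because trainees carry a much heavier load. The article does not support this. The heavier load follows from the Implementation section but not from the abstract. Difficulty can also be lowered for individuals, and both arms receive reminders. No pass rates, and no correlation between adherence and change, are given.

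**Conclusion.** The point holds in a limited form. The rule permits selection that differs by arm, and on its natural reading it conditions a 10-week result on a later event. Whether this produces bias, how much and in which direction cannot be determined from the article. The illustration gives zero under equal selection and about 0.02 to 0.18 SD for assumed pass rates of 60–80% in training against 85–90% in control, with ρ of 0.2 to 0.4. It would be wrong to infer that the trial's main conclusion is compromised, since the intention-to-treat comparison does not use this rule. The planned completer-versus-dropout check describes attrition but does not correct for arm-specific selection on adherence. Separately, the two statements of training frequency make the 80% threshold ambiguous, and those sections must be reconciled before the set can be built.

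**What to change.** 1. Label the protocol-set result as supportive of intention-to-treat wherever both are reported.
2. For the 10-week result, require only the baseline and 10-week assessments; require the 3-month visit only for the maintenance result. Pair this with an analysis of the 10-week contrast that does not delete people for missing T2, such as a baseline-adjusted comparison at T1 or a likelihood-based repeated-measures model.
3. Add, as a supplementary analysis, a complier-average causal effect at 10 weeks, with randomised allocation as the instrument and receipt of training as the exposure. Controls have no access to training until their outcomes are complete, so non-adherence is one-sided. With a yes/no exposure, the estimate is the intention-to-treat difference divided by the proportion of the training arm counted as having received training. State the exclusion restriction: allocation acts on the outcome only through the exposure. Health education common to both arms makes this reasonably plausible. A cut at 80% of sessions also assumes no effect below the cut; using sessions attended assumes linearity instead.
4. State how 80% is counted in each arm, and reconcile the training frequency in the abstract with that in the Implementation section.

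Defining adherence on the shared health education classes alone is not a good substitute. It would admit trainees who did little training and so defeat the set's purpose, and the article mentions a record form for training only.

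The cost is some wording, one change to the 10-week model and one extra analysis using the training records. The complier-average interval is wider: if 75% of trainees count as treated, it widens by roughly 1/0.75 = 1.33 times; at 60%, by 1/0.60 = 1.67 times. It also brings the assumptions named above.
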